## Abstract

**Background:**

Needle-related distress is a common yet poorly recognised and managed problem among haemodialysis (HD) patients. The aim of this pilot study is to test the feasibility and acceptability of the INJECT Intervention—an innovative psychology-based intervention to empower patients to self-manage needle distress with the support of dialysis nurses.

**Methods:**

This investigator-initiated, single-arm, non-randomised feasibility study will take place in a large dialysis service in Adelaide, Australia. Participants will include patients aged ≥ 18 years, commencing or already receiving maintenance HD, recruited through dialysis physicians and nursing staff as individuals believed to be at risk of needle distress. They will be screened for inclusion using the Dialysis Fear of Injection Questionnaire (DFIQ) and enrolled into the study if the score is ≥ 2. The multi-pronged intervention encompasses (i) psychologist review, (ii) patient self-management program and (iii) nursing education program. The primary aim is to evaluate feasibility and acceptability of the intervention from patient and dialysis nurse perspectives, including recruitment, retention, engagement with the intervention and completion. Secondary exploratory outcomes will assess suitability of various tools for measuring needle distress, evaluate acceptability of the nursing education program and measure cannulation-related trauma and vascular access outcomes.

**Conclusion:**

The results will inform the protocol for larger trials addressing needle distress in HD patients.

**Trial registration:**

Australian New Zealand Clinical Trials Registry (ANZCTR): ACTRN12621000229875, approved 4 April 2021, https://www.anzctr.org.au/.

**Supplementary Information:**

The online version contains supplementary material available at 10.1186/s40814-022-00989-2.

## Introduction

Kidney failure is a complex debilitating chronic illness. Severe kidney failure requires kidney replacement therapy (dialysis or kidney transplantation) to sustain life. Although dialysis prolongs life, it has a major effect on patients’ medical, social and psychological wellbeing as they are tied to their treatment 3–7 days per week. In Australia in 2019, approximately 14,000 people received dialysis, 83% of which were treated with haemodialysis (HD) [1].

One of the challenges for haemodialysis patients is frequent and repeated exposure to needles over a long period. Needle-related distress is common amongst general healthcare users [2] and given that the average patient receiving haemodialysis has 2 large bore needles inserted three times per week (312 per year), it is not surprising that needle distress constitutes a significant treatment barrier or burden for many patients [3]. Fear of needles can influence patients’ treatment choice [4, 5] and even result in refusal of treatment [6–8]. Needle distress is often underreported by patients and not routinely assessed by dialysis staff [9, 10]. There are different terms used to describe negative emotional responses that are associated with needle procedures; however, here we use the term needle distress to describe stress, fear and anxiety associated with needle-related procedures.

The *I*mproving Management of *N*eedle Distress during the *J*ourney to Dialysis through Psychological *E*du*C*ation and *T*raining (INJECT) study was informed by findings from several other studies performed by a clinical research group within our local health service. In a point prevalence survey of 551 dialysis patients in a large South Australian dialysis service completed in 2018, 36% of patients reported needle fear, of whom 37% reported that this influenced their treatment choices [3]. In another observational study examining outcomes of vascular access within 6 weeks of starting HD within two South Australian hospitals (*n* = 117), 54% of patients experienced difficulty with insertion of needles [11]. Difficult cannulations are considered a likely contributor in developing needle fear [12] while vascular access has been flagged as a core outcome of critical interest for patients receiving dialysis and other clinical stakeholders [13]. Vascular access complications are one of the major reasons for hospitalisations of patients on HD and are linked with increased mortality, morbidity and cost [13].

We also conducted qualitative interviews with the local health service HD patients (*n* = 15) and nurses (*n* = 17) to explore their experiences, perceptions and opinions regarding needle fear. Both patients and nurses agreed that cannulation can be a traumatic process and that needle fear can directly influence patients’ treatment preferences and engagement, as well as their mental health and quality of life. Both groups also reported a lack of knowledge about needle distress and ways to manage it, emphasising that needle distress is not routinely recognised, validated, assessed or addressed in HD treatment. They also highlighted the critical role of nurses to successful cannulation process and minimising distress. These interviews allowed for the identification of processes involved in preventing, minimising and exacerbating needle fear and distress, including potential management strategies and supports. Data obtained from these interviews informed the development of this pilot patient-led and nurse-supported intervention to address needle fear.

Although studies have investigated alleviating needle distress in non-dialysis settings, few have been conducted in clinical settings [14]. In particular, there are no tested interventions to proactively managing needle distress for those who require longer-term dialysis [10] To address this gap in care, we have developed an educational program based on the principles of cognitive–behavioural therapy (CBT). This program is designed to educate both HD patients and nurses about needle distress and to provide self-management strategies patients can apply to manage fear of dialysis needles.

CBT is a gold standard therapy for anxiety disorders [15–17] and psychological distress [18, 19]. CBT-based strategies have been successfully utilised in a self-help context for a range of mental and physical difficulties [20, 21]. Its basic premise is that our perception of a situation determines how we feel and respond, rather than the situation itself, and that the way we behave can impact the way we feel and vice versa. Thus, in order to reduce distress or unhelpful behaviour, the thoughts that are driving those feelings and behaviours must be identified and challenged. CBT can be delivered face-to-face or digitally; however, the past decade has seen a rapid increase in the digital delivery of CBT interventions. This mode of delivery is a low-intensity, guided self-help [22] that is equivalent in its effectiveness to face-to-face interventions [15, 23].

The educational program is one component of the “*I*mproving Management of *N*eedle Distress during the *J*ourney to Dialysis through Psychological *E*du*C*ation and *T*raining” (INJECT) intervention. The multicomponent intervention (Fig. 1) incorporates (1) psychologist review, (2) patient self-management program and (3) nursing program.

**Fig. 1 Fig1:**
[figure not shown]
Intervention components

The INJECT intervention provides an option to use VR technology as a distraction tool during cannulation. Distraction can aid the management of fear and pain as it diverts a patient’s attention away from unpleasant procedures [24]. Recently, there has been an increase in the number of studies using VR to manage distress and pain associated with needle procedures and chronic conditions [25]. However, the majority of these studies have focused on children and adolescents, while studies involving adults remain limited [25–28]. A recent scoping review explored the use of VR and its effect on the level of engagement in self-care and health-related quality of life of adult patients receiving HD, concluding that it had a positive impact on physical and mental health [29].

The INJECT study is an innovative intervention that aims to better identify needle distress among dialysis patients as part of routine care and empower patients to self-manage needle distress with the support of dialysis nurses. Patients are encouraged to be active participants in their own wellbeing through this opportunity to learn skills to overcome fear of needles. Nurses can improve care delivery by providing support to patients in applying learned strategies to manage needle distress. The goal of this pilot is to assess feasibility and acceptability of each component of the intervention involving patients and dialysis nurses and to use study findings as a guide in the design and implementation of a larger-scale study. We believe that the intervention has a potential to be transferred to other chronic disease patient groups who experience high needle burden as part of treatment, such as receiving chemotherapy.

## Methods

### Study design

The INJECT study is a single-arm, open-label, non-randomised feasibility pilot that will assess a multifaceted intervention to improve needle distress in HD patients. The study intervention components are shown in Fig. 1:Psychologist review (an overall psychologist assessment, completion of baseline questionnaire and explanation of CBT principles + introduction to VR)Patient self-management program (online CBT education modules with an option to use VR as distraction and support from the research officer)Nursing program (nurse education about needle distress and ways to support patients with their self-management).

A suite of novel strategies forms this entire intervention. Each of the components was chosen and developed based on extensive nursing and patient input and will respectively be tested and evaluated. No control group will be employed in this pilot study because there are no inferential comparisons to be conducted. The study flow is presented in Fig. 2.

**Fig. 2 Fig2:**
[figure not shown]
Study flow

This study follows the SPIRIT 2013 [30] guidelines and reporting template (Additional file 1) and CONSORT 2010 statement: extension to randomised pilot and feasibility trials [31] (Additional file 2).

### Participants

HD patients will be recruited from a large South Australian dialysis service. The study will be conducted at 3 metropolitan sites (2 based in hospitals and 1 satellite unit). Inclusion/exclusion criteria are presented in Table 1 below.

**Table 1 Tab1:** Inclusion/exclusion criteria

~ 25 Haemodialysis (HD) patients	
Inclusion	Exclusion
Step 1	
• > 18 years • English speaking • Commencing HD within study timeframe (incident patients) • Already receiving HD • Current AV fistula or graft being used for cannulation • In-patient or outpatient	• Unable to give written consent • Currently receiving psychological therapy/intervention for needle fear/distress • Inability to complete patient self-management modules (e.g. due to literacy, vision impairment, cognitive deficits) • No current exposure to dialysis needles • DFIQ < 2
Step 2	
• HD patients: DFIQ score ≥ 2	

Patients with kidney failure currently receiving, or about to commence, HD will be eligible to participate in the study. The study will be advertised to patients in dialysis units by nurses. Nephrologists and nurses can also promote the study to patients who they suspect may have needle fear or distress and invite them to participate. Nephrologists and nurses will use their clinical judgement and patient review to identify patients that may have the fear of needles. HD nurse practitioner will promote the study to all new haemodialysis patients. The research officer will follow up with the patients and provide them with the patient information sheet and consent form. Following receipt of written informed consent, patients will be screened for inclusion with a validated measure of needle distress: Dialysis Fear of Injection Questionnaire (DFIQ) [9]. Those who score ≥ 2 will be eligible for participation.

This study will be open for recruitment from March 2021 to September 2021.

### Study intervention

The intent of the intervention is not to eradicate distress, but rather to equip patients with skills to more effectively manage distress related to needle fear. The intervention has been co-designed by a multidisciplinary team comprised of researchers, medical professionals, psychologists, nurses and consumer partners. The design of the intervention is flexible and adaptable, and as it does not necessarily require face-to-face contact, it can easily be modified to full online application.

The intervention will have a strong emphasis on skill acquisition and practice, and it will encompass following three components:*Psychologist review*—Following enrolment, patients will receive a 90-min consultation with a clinical psychologist who will be a coinvestigator of the study. This will include an overall psychological assessment, suggestion for ongoing clinical care or referral (if required), completion of baseline questionnaires, provision of an overview of the CBT self-management modules, a demonstration of the VR set and option to test it.*Patient self-management program*—Psychoeducation about needle distress and strategies that patients can apply to manage this will be delivered as a short course in an online learning platform. The course will consist of 6 modules with each module taking 10 to 15 min to complete. The modules were developed by the investigator team with consumer input and consist of videos and written materials explaining CBT principles and strategies tailored to the dialysis needle fear context. The key content summary of learning outcomes is presented in Table 2. Patients will be advised that the online program should be completed within 6 weeks. Although they will be encouraged to progress through the modules at the rate of one module per week, participants can choose to complete the modules at a faster rate if they wish to do so. Patients will be emailed the link to the course which can be accessed on any internet-enabled device such as a computer, laptop, tablet or mobile phone. Modules can be completed during dialysis sessions or at other times suitable to participants. Electronic devices (tablets) will be available for patients to use during dialysis sessions. Paper versions of resources will also be available upon patient request to support the online content.

**Table 2 Tab2:** Key content summary of the patient education program

Modules	Learning outcomes
1. Introduction to needle distress	− What is needle distress, the causes and how it can be experienced - Basic concepts of CBT (cognitive, emotional and behavioural signs of distress) - Ways people may cope with needle distress - Link between distress and avoidance − Self monitoring and why it is important
2. Relaxed breathing	- Rationale and evidence for relaxation - Practical exercise—the skill of relaxed breathing as a way of managing distress or anxiety − Tips for practising/using relaxation
3. Visual imagery	- The use of visual imagery for relaxation - Guided visual imagery exercise − Tips for practising/using visual imagery
4. Cognitive strategies	- How thoughts, beliefs and attitudes influence our experience of distress or anxiety - Guided mindfulness of thoughts exercise − Cognitive strategies for managing unhelpful thoughts
5. Managing difficult emotions	- Acceptance of distress and present moment awareness - Practical exercise: guided mindfulness of emotions - Helpful tips − The use of virtual reality (VR) technology as a distraction (immersion into different environment)
6. Summary	- Review of key strategies - Preparing for slip-ups/setbacks − Further support

Patients will have an option to use VR headsets (oculus Go) at dialysis, as distraction during cannulation if desired. The research team will have several sets with calming, relaxation videos such as ‘Calm on Oculus Go’ ready to be used. Patients will be instructed by the research officer to notify them directly, or via nurses, if they choose to use VR technology so that headsets can be provided.

The research officer will maintain regular weekly follow-ups with participants to track and ensure engagement and progression through the modules, remind participants to use CBT techniques ± VR, and to provide any other support patients may require during the project.*Nursing program*—The nurse education program aims to complement the patient self-management intervention. Nurses will complete the nurse education program prior to the enrolment of patients into the study and be available to support patients with the use of self-management strategies at dialysis. The education program consists of 2 modules that will be available on a local hospital online education platform. This program has been newly developed by the investigator team and teaches best practice techniques for cannulation with minimal trauma, as well as introducing nurses to the INJECT patient program content. Nurses will be taught how to best support patients’ use of self-management strategies during dialysis sessions. Once patients are enrolled in the INJECT intervention, nurses involved in their care will be provided with further education from the project officer, have the opportunity to revisit the online content, and will be given written prompts to refer to at each dialysis session to better support patients with needle distress.

### Data collection

At the enrolment, informed consent and demographic data will be collected. Demographic questionnaire is listed in Additional file 3. A schedule for enrolment, intervention and assessments is displayed as per SPIRIT guidelines in Table 3. Data collected prior to participant’s withdrawal will be used in de-identified form for group analysis and reporting. Course analytics from the online learning platform will enable tracking of patients’ learning and progress through the modules.

**Table 3 Tab3:** Schedule of enrolment, intervention and assessments

	Study period			
	Enrolment	Baseline	3 weeks	6 weeks
		psychological assessment	Post education program completion	
**Timepoint**	**-** ***t***_**1**_	***t***_**0**_	***t***_**1**_	***t***_**2**_
**Enrolment:**				
Informed consent	X			
Eligibility screen- Dialysis Fear of Injection Questionnaire (DFIQ)	X			
Demographics	X			
**Intervention** (6-week duration starting from baseline)				

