### Sample size

As this is a pilot feasibility study that does not propose inferential tests, power calculation is not essential. Our sample size calculation is based on the pragmatics of recruitment and the necessities for examining feasibility among a broad group of patients. We aim to recruit 25 patients. Allowing for a conservative 25% dropout due to death, illness, transplantation, change in dialysis modality and retention rates, we aim to have 20 patients in total.

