### Outcome measures and evaluations

Outcome measures are presented in Table 4. We intend to undertake a thorough process evaluation of each component of the INJECT intervention from both a patient and nurse perspective to obtain a substantial body of feedback about acceptability and feasibility. We anticipate 50% retention rate for patients who are enrolled into the study. We acknowledge that undertaking a self-directed CBT program may not be of interest to all patients with needle fear. Based on previous studies reporting on the use of CBT interventions, dropout rates for psychotherapy range from 16% at the pretreatment phase to 26% at the treatment phase, with some studies reporting an average dropout rate of 47% [35, 36]. Acceptability will be assessed qualitatively, and we anticipate that the intervention will be acceptable from our qualitative approaches. We are unable to put a specific percentage on the reach in this intervention. In our point prevalence survey study, 36% of patients reported needle fear [3]; however, some of them may adapt and will not have an ongoing needle fear. We will use a range of quantitative and qualitative methods including tools to measure needle distress, evaluation surveys and direct interviews to evaluate the experience of patient and nurse participants. Self-devised Patient INJECT evaluation survey and INJECT study satisfaction survey will be pretested with the first 5 patients enrolled in the study. We will capture barriers to recruitment, retention and study completion as well as identify facilitators for successful engagement of nurses and patients. We will record any adverse events to capture safety of the intervention. Participants will have a support from trained dialysis nurses and the Research Officer throughout the study and will be regularly asked about adverse effects as part of the standardised weekly review with the research officer who will be trained to conduct the study. If a patient reports adverse effects, the research officer will discuss this with the participant and with permission, members of the study team. The study team comprises medical and psychology-trained members who will determine the appropriate course of action. The treating nephrologist or the renal psychologist (INJECT investigator) will be involved as appropriate. Finally, we will evaluate clinical outcomes with respect to dialysis vascular access. As this is a feasibility pilot, the assessment of validity or reliability is outside the scope of this study and it will not be assessed.

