
**Table 4 Tab4:** Outcome measures

Outcome domain	Evaluation measures
Primary outcome	
Patient feasibility/acceptability of the intervention	• Patient INJECT evaluation survey: evaluates the feasibility and acceptance of the intervention, identifies which components were most useful or desired (Additional file 4). Self-devised survey uses a 5-point scale (1 = very unsuccessful, 5 = very successful and 1 = not at all, 5 = a lot). A higher score indicates higher success/acceptance of the intervention. • INJECT study satisfaction survey: assesses satisfaction with the content of the online intervention and the ability to understand and utilise presented learning material (Additional file 5). Self-devised survey uses a 5-point scale (1 = disagree, 5 = agree). A higher score indicates greater satisfaction. • Engagement measures: (i) The reach (i.e. proportion of participants who were approached who then agreed to take part in the study) (ii) Retention rates (iii) Completion rates (iv) Online module metrics and analytics—average time spent on page, time to completion of modules, engagement with comments section of platform (v) Reporting to project officer during the study period Semi-structured interviews with study participants to describe their experiences and preferences
Secondary outcomes	
Measures of needle distress	• Blood/Injection Fear Scale (BIFS) obtains specific information on physiological symptoms of anxiety [33]. The scale measures fear of blood/injection on a 5-point scale (1 = strongly agree, 5 = strongly disagree). Lower score indicates higher level of fear. Chronic disease patients’ data for reliability and validity: Cronbach’s α 0.98 • Managing Needle Distress Questionnaire (MNDQ), a self-devised questionnaire to assess patient’s distress (Additional file 6). Self-devised unvalidated survey measures distress on a 5-point scale (1 = agree, 5 = disagree). A higher score indicates greater distress. • Dialysis Fear of Injection Questionnaire (DFIQ) assesses a change in managing needle distress [9]. It measures fear of injection on a 4-point scale (0 = almost never, 3 = almost always). Renal data for reliability and validity: sensitivity 0.88, specificity 0.72, Cronbach’s α 0.87.

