### Planned statistical analysis

Descriptive statistics will be employed to describe the cohort demographic and to analyse survey responses. Qualitative survey data (i.e. responses to open-ended questions) will be extracted using narrative synthesis. Reasons for ineligibility and for non-participation will be reported. Data collected from the DFIQ, MNDQ, BIFS and HADS questionnaires will be analysed by Wilcoxon matched pairs signed-rank tests (Stata software) to calculate changes in scores over the study data collection time points.

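### The DFIQ has no baseline other than its own eligibility screen, so its pre-post change is biased towards improvement by regression to the mean

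*Protocol article*

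**What the plan says.** Under Participants, the DFIQ decides entry: "Those who score ≥ 2 will be eligible for participation". Table 1 lists a lower score as an exclusion.

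In Table 3 the enrolment column carries the "Eligibility screen- Dialysis Fear of Injection Questionnaire (DFIQ". In the assessments block the DFIQ is marked at 3 weeks and 6 weeks, and its t0 cell is empty. The MNDQ, BIFS and HADS are each marked at t0.

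Table 4 lists the DFIQ among the secondary measures of needle distress and says that it "assesses a change in managing needle distress". Planned statistical analysis says that the four questionnaires "will be analysed by Wilcoxon matched pairs signed-rank tests (Stata software) to calculate changes in scores over the study data collection time points".

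Study design states: "No control group will be employed in this pilot study because there are no inferential comparisons to be conducted". The Sample size section says "We aim to recruit 25 patients" and expects 20 after dropout. The section on outcome measures anticipates 50% retention.

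**The concern.** A patient can pass the DFIQ threshold because of stable needle fear, or because that one reading happened to be high. The chance component does not repeat, so the selected group's mean falls at the next administration with or without treatment. Here the selected reading is also the only pre-intervention DFIQ value. A paired test from it to 3 or 6 weeks counts that fall as change, and no control arm is available to subtract it. A later analysis plan cannot recover a baseline that was never measured.

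Two readings of the results are at stake. One is the DFIQ change itself, which may be taken as a signal of benefit. The other is the comparison of instruments: the abstract says the secondary outcomes assess how suitable the various tools are for measuring needle distress. The BIFS, MNDQ and HADS have a t0 value that was not used for selection, so they are much less exposed. The DFIQ could look more responsive than they do purely because of how its starting value was obtained.

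**Working it through.** **Schedule.** Pre-intervention and follow-up measurements according to Table 3:

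| Tool | Enrolment | t0 | 3 weeks | 6 weeks |
|---|---|---|---|---|
| DFIQ | screen, ≥ 2 to enter | – | X | X |
| MNDQ | – | X | – | X |
| BIFS | – | X | X | X |
| HADS | – | X | X | X |

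The only DFIQ change that avoids the screening score is 3 to 6 weeks, and that has no pre-intervention value.

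**The plan's own number.** The Sample size section gives 25 recruited, 25% dropout and 20 remaining. Check: 25 × 0.75 = 18.75, and 20 × 1.25 = 25, so the figures agree to within about one patient. I use n = 20. At the anticipated 50% retention, 25 × 0.5 = 12.5, so I also use n = 12.

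**Assumptions not in the document.** DFIQ scores are normal with a stable population mean. Test-retest correlation ρ is 0.60 to 0.87 (Table 4 gives only Cronbach's α 0.87, which is internal consistency). The share p of screened patients who pass is 36% to 95%. The true intervention effect is zero. The test is two-sided at 5%, so falsely significant improvement has a nominal rate of 2.5%.

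**Formula.** With selection above a cut-off c on one score, the expected spurious improvement in population SD units is

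(1 − ρ) × φ(c) / p, where c is the point exceeded by a share p.

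φ(c)/p is 1.039 at p = 36%, 0.644 at 60%, 0.350 at 80% and 0.109 at 95%. For example, at p = 36% and ρ = 0.60: 0.40 × 1.039 = 0.42 SD. At p = 95% and ρ = 0.87: 0.13 × 0.109 = 0.01 SD.

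**Results.** The false-improvement rates come from simulating the Wilcoxon signed-rank test, 2,000 runs per combination of p, ρ and n, with n = 20:

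| Share passing | Spurious improvement (SD) | Falsely significant improvement |
|---|---|---|
| 36% | 0.14–0.42 | 19%–55% |
| 60% | 0.08–0.26 | 10%–23% |
| 80% | 0.05–0.14 | 5%–9% |
| 95% | 0.01–0.04 | 3%–4% |

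With n = 12 and 36% passing, the false-improvement rate is 11% to 31%.

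**With a DFIQ at t0 as reference.** If the t0 error is independent of the screening error, the simulated null change lies between −0.005 and +0.008 SD and false improvement is about 2% to 3%.

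**If the screening error persists to t0.** Suppose the correlation is 0.8 between screen and t0 and 0.6 between screen and 6 weeks, with 36% passing. The residual spurious change from t0 to 6 weeks is (0.8 − 0.6) × 1.04 = 0.21 SD. That is half of the 0.42 SD seen from the screen.

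**The case against.** The strongest reply is that little hangs on this outcome. DFIQ change is secondary and exploratory, and the primary aim is feasibility and acceptability. The progression criteria rest on recruitment, retention, completeness of outcome data, perceived usefulness of components and interviews. That stands, and it limits the weight of the point. It does not remove it: the analysis section still plans paired tests on the DFIQ, although Study design disclaims inferential comparisons, so a spurious significant result could be reported.

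The second reply is that the size is unknown and may be small. This also stands. A reader might take 36% as the pass rate, because that figure is the reported prevalence of needle fear. It comes from a general dialysis survey and is not a DFIQ result. Clinicians invite suspected cases, which would raise the pass rate, although the study is also advertised generally and promoted to all new haemodialysis patients. The article does not say whether the threshold applies to a sum or a mean of items, so the severity of the cut cannot be worked out, and the normal model for a bounded scale is unverified.

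Three stronger readings should be set aside:

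- A reader might infer that an inflated DFIQ change would make the next trial too small. The article names no endpoint for a larger trial and does not say that the pilot's change will size it.
- A reader might take the remark that "some of them may adapt and will not have an ongoing needle fear" as an admission of regression to the mean. It explains why reach cannot be given as a percentage, and it describes real adaptation rather than selection on a chance high score.
- A reader might expect a t0 score to cure the problem completely. It does so only if the screening error has gone by t0, and the interval from enrolment to t0 is not stated.

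**Conclusion.** The point holds. Using the eligibility score as the sole pre-intervention DFIQ value, without a control group, biases DFIQ change towards improvement for any test-retest correlation below 1. It may also flatter the DFIQ against the tools that have a separate t0 value.

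The direction follows from the design. The size cannot be fixed from the article: under the stated assumptions it runs from negligible, if nearly everyone screened passes, to substantial, if about a third do. It should be corrected because the remedy is cheap and the missing measurement cannot be made up later. It does not threaten the primary feasibility aim or the progression decision.

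**What to change.** Add the DFIQ at t0 in Table 3, completed with the other baseline questionnaires and before the content of the psychologist consultation begins. State in Planned statistical analysis that t0 is the reference for DFIQ change and that the screening score serves eligibility only. Report the shift from screen to t0 as a partial indication of regression to the mean.

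Add a sentence saying that this reduces the selection artefact, removes it fully only if the screening error does not persist to t0, and leaves natural adaptation in place. Where a t0 value cannot be obtained, report DFIQ change descriptively with the same caveat.

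The cost is one extra short questionnaire at a visit where baseline questionnaires are already completed.
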